##### Component 2 – Paper pamphlet

A paper pamphlet provided by reception staff to patients whose health card does not indicate that they are registered donors will aim to directly address barriers and enablers to registration. The pamphlet will also be available in each waiting room for any patient to take if they wish. The pamphlet will provide visual and written instruction on how to check donor status and how to register securely online, will provide information about others’ approval using credible sources (using photos, signatures and stories from family physicians and local patients), will facilitate social comparison with other local patients, will persuade them of their capability to register by indicating how easy it is and how little time it takes, and then providing information of vicarious and salient consequences of registering (impact on organ transplant recipients), information on social and environmental consequences (impact on the wider community), and information on emotional consequences (how they may feel once registered).

##### Component 3 – Providing immediate opportunity to register

A secure Internet-enabled tablet (i.e., an iPad) will be added in each waiting room to give patients the immediate opportunity to register for organ donation online via a secure provincial website. Adding the tablet also aims to address beliefs about capability to register and acts as a prompt/cue to register, focusing their attention and prioritizing registration while they wait. Table 3 provides a further overview of intervention as per TiDIER criteria, and online additional materials provides detailed mapping of BCTs to theoretical domains informed by interview results). All materials will be in English only for this intervention. The location of the materials will be tailored according to the family physician office’s preferences.

**Table 3 Tab3:** Overview of the RegisterNow-1 intervention, as per Template for Intervention Description and Replication (TiDIER) criteria

TiDIER criteria	Description of intervention and quality control procedures
Brief name	RegisterNow-1 intervention
Why?	Patients are often unsure if they registered for organ donation. Many patients support organ donation but have not prioritized it and may not get around to it. Providing immediate opportunity to register for organ donation would address this barrier and leverage those already motivated to register
What materials?	Pamphlets designed to address previously identified barriers and enablers to organ donation registration, Internet-enabled tablet, and training material for office staff
What procedures?	Reception staff will check health cards for donor status, use a standard script to provide a pamphlet to patients and suggest to those that have not yet registered for organ donation that they can do so using the tablet in the waiting room. The pamphlet will describe ways the patient can register for organ donation (e.g., use the Internet-enabled tablet in the waiting room). Behavior Change Techniques (BCTs) are described in Table 2
Who provided?	Reception staff
How?	Face to face, paper and electronic
Where?	Family physician office waiting room
When and how much?	The intervention will be available between 2 and 14 weeks in duration (depending on the randomly allocated start date). For a given patient, they are likely only to be exposed to the intervention once unless they have a repeat visit during the period in which their practice is delivering the intervention
Tailoring	Reception staff can adapt the script to their practice. The content of the pamphlet can be minimally tailored according to the family physician office to include the name of the practice, the name of the physicians at the practice, a photo of the physicians and their signature. The location of the Internet-enabled tablet and additional pamphlets within the waiting room can be tailored by the practice staff

### Enhancing the fidelity of delivery and adherence to the intervention

We will conduct a setup meeting within each family practice, involving family physicians and reception staff. Nurses and nurse practitioners may also be involved depending on the site. This meeting will involve describing the intervention, roles and responsibilities, presenting the materials, clarifying the start date and duration of the intervention and trial design, and tailoring the location of the tablet and the patient-focused pamphlets using practice-specific content (photos, logos, signatures).

Following the setup meeting, a research assistant and/or researcher will conduct a 1-h in-person training session with reception staff in each office, to clarify how the intervention is delivered, the start date, the duration of delivery, and provide instructions to reception staff on how to check all patients’ health cards for their donor registration status at the time of the patient visit, what to say to patients, provide an overview of the content of the pamphlets that they are asked to provide, and an overview of how to setup and use the tablet. These will also be provided in writing for any reception staff not able to attend the session. The in-person training session will occur within 4 weeks prior to the intervention start time in each office. Staff training will be based on the principles of Social Cognitive Theory, focusing on practicing and rehearsing to develop a new routine and self-efficacy to deliver the intervention and providing information on health and social consequences to support the need for the intervention and motivation to deliver it [23]. Staff will also receive paper-based descriptions of suggestions for how to address questions that may arise from patients. For example, some patients may ask for more details regarding the rules around family vetoing deceased organ donation. This booklet will also encourage physicians to talk to their patients about organ donation if appropriate.

On the first day of crossing into the intervention condition, the research assistant will bring all materials to the practice and set up the tablet. A research assistant will contact a representative from each family physician clinic by phone or email the week prior to beginning the intervention period to confirm readiness. Offices will then be contacted again every week until the end of the trial to promote ongoing fidelity of delivery, remind them (prompts/cues) and resolve emerging issues (problem solving). Problems that may emerge may include technical issues such as the tablet not functioning or running out of pamphlets. We will provide each member of family physician office staff who participated in the trial with an honorarium of CAD$50 upon completion of the trial.

### Control condition

The nature of the stepped-wedge design is such that practices will all begin in the control condition and then sequentially cross to the intervention condition for the remainder of the study period. We will ask family physicians and reception staff to continue with their usual practice while in the control condition until the date that they have been randomized to cross to the intervention condition. Intervention materials and training (e.g., pamphlets, tablet) will not be provided until their site crosses into the intervention arm.

### Outcomes

The primary outcome is the proportion of all patients aged 16 years and older who visited the office during each 2-week interval who are registered for deceased organ donation at 7 days following the family physician visit. We chose 7 days to ensure that patients have the opportunity, should they wish, to discuss their decision to register with their family or friends. However, we expect and have designed the intervention so that most of the registrations take place immediately (same day) during their family physician clinic visit; this is consistent with the observed barriers to registration. We designated prevalence of donor registration (rather than incidence of new registrations) as the primary outcome for the trial as it was important to measure the net effect of our cluster-level intervention on the overall prevalence of donor registration among all patients with visits to their family physician. Secondary outcomes are the proportions of unregistered patients aged 16 years and older who newly register for deceased organ donation within 7 days of visiting the family physician clinic, as well as at 1 day, 14 days and 30 days post visit.

### Study timeline

We will recruit all six family physician offices prior to the start of the intervention (see Fig. 1). Given that there is a delay for the records to enter the administrative databases, we will only be able to assess baseline information and outcomes at the end of our trial.

**Fig. 1 Fig1:**
[figure not shown]
Stepped-wedge design

### Sample size

We would consider an absolute increase of 10% or more in the proportion of patients who are registered organ donors at 7 days post encounter to be both clinically important and realistic to achieve. Our sample size of six clusters (10,500 patients in total) achieves 80% power to detect a 10% absolute difference assuming a control proportion of 0.5 using a two-sided test at the 5% level of significance [24]. Our calculation assumes an intracluster correlation coefficient of 0.06, as calculated from our previous work [Institute for Clinical Evaluative Sciences KDT. Feasibility of organ donor registration in family physician offices across Greater Toronto Area. Internal report: 2015; unpublished.], an average of 250 patient encounters per site in each 2-week interval, and a cluster autocorrelation coefficient of 0.8 to allow for a 20% decay in the strength of the correlation in repeated measures over time [24]. The percentage of registered donors in the control condition is conservatively assumed to be 50% to allow for a higher prevalence of registered donors in our participating offices than the provincial average. No adjustment is made for cluster attrition as the risk of attrition is extremely low, and all outcomes will be assessed from routinely collected sources, regardless of any dropout. Given some uncertainty around parameter estimates required for the stepped-wedge sample size calculation, sensitivity of our detectable effect size to a range of alternative assumptions is presented in Table 4. The results show that across a range of control arm proportions (from 0.4 to 0.5), average cluster sizes (from 100 to 400) and cluster autocorrelation coefficients (from 0.8 to 0.95), our sample size of six practices will achieve 80% power to detect absolute increases of between 5 and 11%.

**Table 4 Tab4:** Sensitivity analysis

Control proportion	Intervention proportion	Within-period ICC	Cluster autocorre-lation	Average cluster size per period	Absolute increase in proportion
0.5	0.61	0.06	0.8	100	0.110
	0.6	0.06	0.8	250	0.100
	0.59	0.06	0.8	400	0.090
	0.59	0.06	0.95	100	0.090
	0.565	0.06	0.95	250	0.065
	0.56	0.06	0.95	400	0.060
0.4	0.51	0.06	0.8	100	0.110
	0.5	0.06	0.8	250	0.100
	0.49	0.06	0.8	400	0.090
	0.49	0.06	0.95	100	0.090
	0.465	0.06	0.95	250	0.065
	0.46	0.06	0.95	400	0.060
0.45	0.56	0.06	0.8	100	0.110
	0.55	0.06	0.8	250	0.100
	0.545	0.06	0.8	400	0.095
	0.54	0.06	0.95	100	0.090
	0.515	0.06	0.95	250	0.065
	0.51	0.06	0.95	400	0.060

Sensitivity analysis showing detectable difference with a sample size of six practices, expressed as an absolute increase in proportions, with 80% power using a two-sided test at the 5% level of significance

### Recruitment

We will recruit a convenience sample of practices from within our network of family physician office contacts within the London, Ontario (41% donor registration rate) and Stratford, Ontario communities (46% donor registration rate). A collaborating family physician will send an introductory email to potential family physician contacts, inviting them and their practice to consider participating. We will then arrange an in-person meeting with family physicians from interested sites to introduce our study and obtain written agreement from family physicians and offices agreeing to participate that meet our eligibility criteria.

### Sequence generation (i.e., randomization)

Each of the six participating clinics (clusters) will be randomly allocated to six different starting dates for the intervention (steps). A statistician blinded to cluster identity and not involved in the intervention delivery will generate the allocation sequence using computer-generated random numbers. The timing of the transition from control to intervention will not be communicated to the offices and the research coordinator until 2–4 weeks prior to transitioning (to balance minimizing risk of bias during control periods with the need for planning, training and setup for implementing the intervention) (see Fig. 2 for the SPIRIT Figure). The research coordinator will communicate intervention starting times with the participating clinics.

**Fig. 2 Fig2:**
[figure not shown]
Trial schedule of enrollment, intervention and assessment (as recommended by SPIRIT; Figure displaying schedule of enrollment and interventions)

### Blinding

Family physicians and their staff will be aware of the intervention they provide during the intervention periods (i.e., they are not blinded). However, the timing of allocation to intervention will be concealed from investigators, participating physicians and their patients. In addition, the biostatistician performing the analysis will be blinded to the identity of the sites. In both the control and intervention condition, family physician offices will have a poster in the waiting room that the site is currently participating in a research study and feature a link for more information, but patients will not be explicitly told which condition they are in.

### Data collection methods/data management

We will ascertain baseline and outcome information from healthcare administrative databases housed at the Institute for Clinical Evaluative Sciences (ICES). Under section 45 of Ontario’s Personal Health Information Privacy Act, ICES is considered a prescribed entity. Health information custodians, such as physicians, can disclose personal health information to ICES without patient consent for the purpose of research. These databases can be linked via encoded identifiers. Specifically, we will use our list of recruited family physicians to link to the Ontario Health Insurance Plan (OHIP) billing datasets to identify the patients who visited our recruited family physicians and the dates at which they visited. We will then use the Registered Persons Database to obtain patient demographic information and their donor registration information (including date of registration).

### Additional analyses

We will also conduct several pre-specified subgroup analyses to examine the differential effect of our intervention by age (younger (≤40 years) vs. older (>40 years)) and sex (male vs. female). We hypothesize that our study may be more effective among older individuals who tend to have more concerns about their eligibility to register for organ donation (e.g., too old to register). We will explore differential intervention effects by sex but hypothesize that there are no differences between male and female.

### Statistical methods

We will describe site and patient demographic characteristics across all control and intervention periods using descriptive statistics. All analyses will be conducted according to the intention-to-treat principle. We will analyze the primary and secondary outcomes at the individual patient-level using mixed-effects logistic regression accounting for the stepped-wedge design as described by Hooper et al. [25]. The model will include intervention status and time as fixed effects and will include a random intercept and slope for time defined at the level of the family physician office. The inclusion of these two random effects accounts for within-period and between-period intracluster correlations. To correct the potential inflation of the type I error rate due to small number of clusters, we will use the Kenward and Roger method [26]. To express the estimated effect of the intervention as an absolute difference, we will fit the regression model with the binomial distribution and an identity link function; in case of non-convergence, the log or logit link function will be used and results will be reported as either rate ratios or odds ratios together with 95% confidence intervals. With only six offices in our trial, there may be differences in the characteristics of patients visiting the offices during the periods of interest that may confound the intervention effect. We will adjust for three patient-level covariates: age, sex and neighborhood income quintile. Our previous studies showed that younger age, female sex and higher income quintile were associated with organ donor registration [27]. Subgroup analyses will be conducted either as stratified analyses or by including interactions between each subgroup variable, time and the intervention indicator. We will conduct all analyses using Statistical Analysis Software (SAS) version 9.4 and statistical significance will be assessed at the 5% level.

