## Methods

### Participants, interventions and outcomes

#### Study setting

We will conduct the trial in six family physician offices located in Ontario, Canada. Key components of the trial are described in Table 1. As of 2008, Ontario’s organ and tissue donor registry became affirmative only (i.e., recording only “yes” responses). Citizens of 16 years of age and older can register online or can mail in a Donor Registration Form. It is also provincially mandated that individuals be asked about organ and tissue donor registration with all health-card related transactions, driver’s licence renewals and photo ID applications at ServiceOntario centers. Those who choose to register can also select to donate for research purposes and exclude certain organs or tissues from donation. While citizens can also withdraw their registration whenever they like, less than 0.1% of the registered population withdraws its registration each year.

**Table 1 Tab1:** Key characteristics of the trial

Trial characteristics	Definition
Cluster (unit of randomization)	Family physician office (a total of 6)
Number of sequences (steps)	6 (one office per sequence)
Duration of trial	14 weeks
Number of measurement periods	7 (length of each period is 2 weeks)
Individuals	Patients eligible to register for deceased organ donation and visiting a family physician at any time during the study
Timing of start of exposure	Individuals are exposed in a continuous and gradual process as they present to their family physician offices
Duration of exposure	All individuals are exposed for a short period during their visit to the physician office
Measurement	Repeated measurements are taken from mostly different individuals in each period; it is possible that a very small proportion of individuals will have repeat visits to their family doctors but because no identifying information will be collected, such individuals will be included in the analysis as independent individuals
Total number of clinics (clusters)	6

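### The primary prevalence model leaves out each patient's registration status before the visit, which the linked dates supply, and so has little power for effects well below 10 points

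*Protocol article*

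**What the plan says.** The Outcomes section defines the primary outcome as "the proportion of all patients aged 16 years and older who visited the office during each 2-week interval who are registered for deceased organ donation", with status read one week after the visit. It explains the choice: "We designated prevalence of donor registration (rather than incidence of new registrations) as the primary outcome", so as to capture the net effect on everyone who attends. Status before the visit enters only the secondary outcomes: "Secondary outcomes are the proportions of unregistered patients aged 16 years and older who newly register for deceased organ donation within 7 days", with further time points at 1, 14 and 30 days.

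Statistical methods specifies intervention and time as fixed effects, office-level random effects and a small-sample correction. It gives the reason for covariate adjustment with six offices: "there may be differences in the characteristics of patients visiting the offices during the periods of interest that may confound the intervention effect". The list that follows is closed: "We will adjust for three patient-level covariates: age, sex and neighborhood income quintile".

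Data collection methods/data management takes visit dates from billing records and, from the Registered Persons Database, "patient demographic information and their donor registration information (including date of registration"). Study setting reports that "less than 0.1% of the registered population withdraws its registration each year".

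**The concern.** With withdrawals that rare, being registered at day 7 is almost exactly the sum of two parts: registered before the visit, and newly registered within 7 days. A waiting-room intervention acts on the second part. Repeat visitors, and people prompted through someone else, are the exceptions. The first part makes up most of the outcome, and its chance variation goes into the standard error.

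The protocol adjusts for age, sex and income because they are associated with registration. They are proxies for a quantity that the trial holds directly and already needs for its secondary outcomes. At stake is the ability of the deciding analysis to see an effect smaller than the 10-point target. A null result would feed into the decision on a larger provincial roll-out, which the Discussion names as the trial's purpose.

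**Working it through.** **Inputs from Sample size and Table 1.** 6 offices, 7 periods, 250 patients per office-period (m), ICC 0.06, CAC 0.8 (Table 4 goes to 0.95), control proportion 0.5, two-sided 5%.

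**1. The protocol's own figure.**
- Individually randomized, 0.50 vs 0.60 at 80% power: 388 per arm, 776 in total.
- Clustering factor: 1 + 249 × 0.06 = 15.94.
- Correlation of office means between periods: r = 250 × 0.06 × 0.8 / 15.94 = 0.753.
- Stepped-wedge factor for 6 steps: 18(1 − r)(1 + 6r) / [35(2 + 6r)] = 0.1076. The product is 15.94 × 0.1076 = 1.715.
- 776 × 1.715 = 1,331 per period, and 1,331/250 = 5.3 offices, rounded up to 6. Then 6 × 7 × 250 = 10,500. The stated figure is reproduced.

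**2. What stays in the error term** (outcome variance 0.25).
- Stable office SD: √(0.06 × 0.8 × 0.25) = 11.0 points, largely absorbed by the office intercept.
- Office-by-period SD: √(0.06 × 0.2 × 0.25) = 5.5 points, not absorbed.
- Sampling SD of an office-period mean: √(0.94 × 0.25/250) = 3.1 points, not absorbed.

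**3. Planned analysis.** Let s² be the outcome variance, a = s²[ICC(1 − CAC) + (1 − ICC)/m] and b = s² × ICC × CAC. Generalized least squares on office-period means with fixed periods gives, for this layout, Var = 6a(a + 7b)/(35a + 140b).
- CAC 0.8: a = 0.00394, b = 0.0120, Var = 0.001144, SE = 3.38 points.
- CAC 0.95: a = 0.00169, b = 0.01425, Var = 0.000501, SE = 2.24 points.
- Detectable difference at 80% power, 2.80 × SE: 9.5 and 6.3 points. With the two conditions' variances averaged (s² = 0.245): 9.4 and 6.2.
- Power at 10 points, CAC 0.8: Φ(0.10/0.0338 − 1.96) = 84%. With a t reference on 29 to 40 df it is about 82%.
- Power at 3.5 points: 18% (CAC 0.8) and 35% (CAC 0.95).

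**4. Why 3.5 points.** The Background cites a primary-care trial in unregistered patients with 22% vs 15% new registrations. That is 7 points among the unregistered, and 7 × 0.5 = 3.5 points of all visitors at 50% prevalence. The 10-point target would need 10/0.5 = 20% of all unregistered visitors to register because of the intervention.

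**5. Change in status on all 250 visitors.** The protocol gives no background 7-day registration rate q and no ICC or CAC for new registration, so these are assumptions. The variance is averaged over conditions: s² = [q(1 − q) + (q + d)(1 − q − d)]/2. Example with q = 1%, d = 3.5 points, ICC 0.06, CAC 0.8: s² = (0.0099 + 0.0430)/2 = 0.0264, SE = 0.0338 × √(0.0264/0.25) = 1.10 points, power = Φ(0.035/0.0110 − 1.96) = 89%.

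| q, all control visitors | ICC | CAC | Detectable difference (points) | Power at 3.5 points |
|---|---|---|---|---|
| 0.2% | 0.01 to 0.06 | 0.8 | 0.9 to 2.1 | over 99% to 96% |
| 1% | 0.01 to 0.06 | 0.8 | 1.5 to 2.9 | over 99% to 89% |
| 2.5% | 0.01 to 0.06 | 0.8 | 2.1 to 3.9 | 99% to 73% |
| 7.5% | 0.01 to 0.06 | 0.8 | 3.3 to 5.8 | 84% to 43% |
| 1% | 0.06 | 0.5 | 4.8 | 61% |

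The 7.5% row is the cited trial's 15% control rate applied to an unregistered half. Apart from the 82%, all power figures use the normal approximation.

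**The case against.** Prevalence was chosen deliberately, with a reason. New registration within 7 days is already a secondary outcome under the same model, and at a 3.5-point all-visitor rise it would itself have 92% to over 99% power (background 0.5% to 5% of the unregistered, ICC up to 0.06, CAC 0.8). Both points stand as mitigation. But the net-effect argument supports the estimand, which adjustment keeps, and a secondary outcome restricted to unregistered patients does not decide the trial.

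A change score has its own difficulties. The outcome is rare, its variance differs by condition, repeat visits need rules, and a relative prompted to register before their own visit is not counted. These stand as costs.

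A reader might infer four stronger things that the documents do not support:
- **That all between-office and between-period variation obscures the effect.** The office intercept and fixed time effects deal with stable differences and common shifts. Only the office-by-period part and sampling error remain.
- **That chance shifts in who attends bias the result.** They add variance, which the sample size already allows for through the CAC.
- **That the trial is underpowered for its target.** It reaches about 84% for 10 points.
- **That adjustment secures about 90% power or more at 3.5 points.** That needs a background rate of 1% or less with ICC up to 0.06 and CAC 0.8. The cited trial's own control rate gives 43% to 84%.

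**Conclusion.** The point holds as a loss of efficiency in the deciding analysis. The closed covariate list omits the strongest available predictor of the outcome, which is already held for every patient. The planned analysis meets its 10-point design target but has only 18% to 35% power for a 3.5-point rise.

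At CAC 0.8, using pre-visit status lowers the detectable difference from about 9.4 points to roughly 1 to 4, with power at 3.5 points of about 73% to over 99%, for background rates of 0.2% to 2.5% and ICC 0.01 to 0.06. The gain shrinks at a 7.5% background (43% to 84%) or at CAC 0.5 (61% with a 1% background and ICC 0.06). Its direction is well supported across the scenarios tabulated. Its size rests on rates and correlations that the protocol does not give.

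**What to change.** Keep 7-day prevalence among all visitors as the estimand and make the primary analysis baseline-adjusted. Two forms would serve: pre-visit registration status as a covariate, or the change in status from before the visit to day 7, modelled on the absolute scale. In either form, keep the same period, intervention and office terms, the small-sample correction and the three listed covariates, and use a variance estimate that allows for unequal variance by condition.

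Take baseline as status before the patient's first visit in the trial, or analyse first visits only, so that registrations from an earlier exposed visit are not adjusted away. Report the planned analysis without pre-visit status as supportive. Fix the wording before linked outcome data are examined; Study timeline says that baseline and outcomes are assessed only at the end of the trial.

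The cost is analysis work, with no new data and no new offices. Repeat visits, which Table 1 treats as independent individuals, must be linked through the encoded identifiers. A rare outcome must be handled in the model. Any registration that the intervention prompts before a patient's own first visit is not counted.
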